### Fidelity

Fidelity has four defined components: design of the intervention, training in the intervention, monitoring the delivery of the intervention and monitoring its receipt. As it is essential to maintain fidelity, the treatment will be manualised and intervention staff will be appropriately trained to adhere to the treatment guides. Training in the intervention includes role-playing, which facilitates competence in the delivery of the intervention. As part of the training, an intervention training manual has been developed that will be used in the intervention and controls. Delivery of the intervention will be monitored through patient cards and video and audio recordings of patient session. Supervision will also be used to maintain fidelity. The standard operating procedures will contain supervision protocols. The receipt of the intervention will be monitored through patient record cards and interviews. Overall fidelity will be assessed with a comprehensive intervention fidelity guide (CIFG) [58].

### Randomization

A computer generated block randomization will be used to assign clinics to either intervention or control arm (as shown in Fig. 4).

**Fig. 4 Fig4:**
[figure not shown]
Procedure and study flow diagram

### Allocation concealment

A statistician on the study based in South Africa will maintain concealment of allocation.

### Blinding

Participants will not be blind to treatment. Research assistants who administer the outcome measures will be blinded to the assignment of clinics to intervention and control. Blinding will be achieved by retaining the same assessors at a site from the baseline, the 3,6 and 12 months assessments. In order to minimise assessment bias, assessors will not have access to the data collected at previous assessments. The Principal Investigator will be not be blinded to clinic status as he will be a trainer on the interventions.

### Visits

At the baseline visit, the AUDIT, DUDIT, SAMISS, IHDS, WHOQoL HIV and WHODAS 2 will be administered. The AUDIT, WHOQoL HIV, and WHODAS will be administered at 3, 6, and 12 months. The CD4 count and viral load will be measured at baseline, 3, 6 and 12 months to assess adherence. The MSPSS, COPE-13, and the Davison Trauma Scale will assess social support, coping and resilience at baseline and 12 months, and included as moderator variables in the analysis

### Statistical analysis

#### Sample size

A meta-analysis suggested that a clinically significant difference in negative status on the AUDIT between brief intervention and control of 13% [59]. Shersten et al. [60] describe intra-cluster correlation coefficient in human subjects to be between 0.01 and 0.02 and assumed the intra-cluster correlation in this study to be 0.02. A total of 16 clusters (8 clusters per group) to achieve 80% power to detect a mean difference of 2.5 (with precision of ± 0.45) between the treatment condition means when the standard deviation within a cluster is 4 and the intra-cluster correlation are 0.02 and a significance level of 0.05.

An estimated sample size of 180 patients (90 in the intervention group and 90 in the control group) will be required to detect a difference of 13% between intervention and control groups taking into account the design effect of 1.56. Assuming an attrition rate of 30% (as identified in the pilot study), a total sample size of 240 will be required. Fifteen participants will be randomly selected (with equal probability) at each clinic from a patient number list.

Analysis of covariance (ANCOVAs) and mixed effects linear regression models will be performed for all continuous variables. Generalised linear mixed effects logistic regression model will be performed for binary outcomes. All analyses will allow for within-clinic clustering.

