#### Control

An adapted version of the mhGAP intervention guide (the alcohol section) will be administered to participants at 8 clinics. The session will also focus on providing feedback on the AUDIT score, the CD4 count, viral load, and on functioning and quality of life. This intervention is expected to last one hour (based on our experience in the pilot study). At 3 and 6 months, the control intervention will be re-administered and outcomes assessed with the final assessment done at 12 months.

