## Discussion

In this study it is hypothesized that an adapted MI/CBT intervention will lead to a significant reduction in alcohol use in PLWHA. It is further hypothesized that reduction in alcohol use will lead to improved function as measured by the WHODAS 2.0, improved quality of life as measured by the WHOQoL HIV, and improved adherence to HAART as measured by the CD4 and viral load. This study further seeks to establish whether registered general nurses in primary health care facilities in Zimbabwe will be effective in providing the MI/CBT intervention to reduce alcohol use and improve patient engagement with treatment.

We will test the effectiveness of an MI/CBT intervention that can be used by RGNs for alcohol reduction in PLWHA. If successful, the intervention will be implemented in HIV clinics in Zimbabwe and other settings where general nurses oversee HIV treatment. We hypothesize that patients may view their ability to return to work as important and this may motivate them to adhere to the treatment. Improved quality of life has been shown to improve adherence in other studies.

Given that most behavioural interventions for alcohol use have been developed within a Western framework, the use of an adapted intervention in this study will inform us about its effectiveness in reducing alcohol use in PLWHA in a resource limited setting. In resource rich environments, inpatient and outpatient services for addictions are usually widely available. However, in Zimbabwe, as in many other resource-limited settings, inpatient management of AUDs may be unaffordable for the majority. Outpatient care, if available, is the rule rather than the exception.

To the authors’ knowledge, no published study from Zimbabwe has examined functioning and quality of life in PLWHA with AUDs. Improvement in functioning and quality of life are key aspects to address in this population. Quality of life has been shown to improve upon initiation of HAART (http://www.stata.com) and studies in other countries have documented an improvement in adherence with an improvement in quality of life [61]. Over a quarter of 15–49 year olds in sub-Saharan Africa are living with AIDS [62]. Given that this is the most productive age group in the community, improving functioning will likely have positive socio-economic impacts on the community.

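### The 13% difference behind the sample size comes from brief intervention versus control and is not supported as a target for 16-session MI/CBT versus repeated mhGAP

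*Protocol article*

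**What the plan says.** The Sample size section gives two targets.

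- **Binary target.** It cites a meta-analysis: "A meta-analysis suggested that a clinically significant difference in negative status on the AUDIT between brief intervention and control of 13" per cent. The next paragraph applies the same figure to this trial. It puts the need at 180 evaluable patients, split equally between the arms, and says that this number "will be required to detect a difference of 13% between intervention and control groups". A design effect of 1.56 is included.
- **Mean target.** "A total of 16 clusters (8 clusters per group) to achieve 80% power to detect a mean difference of 2.5" points, with within-cluster SD 4, ICC 0.02 and significance level 0.05. No source is given for the 2.5 points, and this is the only place where a power is stated.

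The Control section describes the comparator as the alcohol part of the mhGAP guide, lasting about an hour. It adds: "The session will also focus on providing feedback on the AUDIT score, the CD4 count, viral load, and on functioning and quality of life". It continues: "At 3 and 6 months, the control intervention will be re-administered". The Intervention section gives the experimental arm 16 sessions, eight at the start and four each at 3 and 6 months.

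The primary outcome (Primary outcome tools; Outcome measures) is the AUDIT score or its change from baseline, not AUDIT-negative status. The Aims name no comparator in the effectiveness aim. In the Discussion, "it is hypothesized that an adapted MI/CBT intervention will lead to a significant reduction in alcohol use in PLWHA", again with no comparator.

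**The concern.** A target difference should refer to the contrast that is randomised. The 13% describes brief intervention against some control. In this trial, a treatment of the brief-intervention kind sits in the control arm, and the experimental arm is longer than a brief intervention. The figure therefore moves between two different comparisons, and the article offers no argument for the move.

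Two things are at stake. First, the 180 patients are justified by a difference that nobody has argued is expected, or important, for MI/CBT over mhGAP. Second, the design estimates only the benefit of MI/CBT beyond mhGAP, whereas the aim and hypothesis read as an effect of MI/CBT in itself. If both arms reduce drinking and the arms do not differ significantly, the result could be taken to mean that nurse-delivered MI/CBT does not work. The Discussion ties implementation to success.

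**Working it through.** **1. The two contrasts side by side**

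| | Source of the 13% | This trial |
|---|---|---|
| Treated side | Brief intervention | MI/CBT, 16 sessions |
| Comparator | Control, not described | mhGAP alcohol section, about 1 hour, AUDIT feedback, repeated at 3 and 6 months |
| Outcome | AUDIT-negative status | AUDIT score |

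No row matches.

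**2. Direction of the error**

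Suppose that, relative to the source's control, MI/CBT delivers a × 13 points and mhGAP delivers b × 13 points. The between-arm difference is then (a − b) × 13. The article gives neither a nor b. Purely as assumptions:

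- a = 1, b = 0.5: 6.5 points
- a = 1.5, b = 0.5: 13 points
- a = 1.5, b = 0.25: 16.25 points

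The difference can be below, at or above 13.

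**3. Does the plan's 180 follow from the 13%?**

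I used the two-proportion formula (pooled variance under the null, two-sided 0.05, 80% power) multiplied by 1.56. The AUDIT-negative rate in the control arm is not given, so a range is assumed.

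| Control rate | n per arm before clustering | × 1.56, rounded up |
|---|---|---|
| 0% | 56 | 88 |
| 10% | 127 | 199 |
| 20% | 180 | 281 |
| 30% | 215 | 336 |
| 40% | 230 | 359 |
| 50% | 228 | 356 |

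The stated 90 per arm is met only near the degenerate case of 0% versus 13% (or 87% versus 100%). With 90 per arm and a cluster-level t-test on 14 df, power for a true 13-point difference at control rates of 10–50% is about 32–53% with design effect 1 + (11.25 − 1) × 0.02 = 1.205. With the plan's 1.56 it is about 26–43%. This shortfall is an arithmetic problem of its own. It would exist even if the 13% were the right target, and the present point does not depend on it.

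**4. The sizing on the AUDIT score**

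Inputs from the Sample size section: 8 clinics per arm, within-clinic SD 4, ICC 0.02, alpha 0.05 (two-sided assumed). Evaluable patients: 180 as stated, or 240 × 0.70 = 168 under the stated 30% attrition. Per clinic: 180/16 = 11.25, or 168/16 = 10.5.

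- Between-clinic variance = 16 × 0.02/0.98 = 0.327
- SE = √[2 × (0.327 + 16/m)/8], with m patients per clinic
- m = 11.25: √[2 × (0.327 + 1.422)/8] = 0.661
- m = 10.5: √[2 × (0.327 + 1.524)/8] = 0.680

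Power is from the noncentral t with 14 df and noncentrality difference/SE:

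| True difference (AUDIT points) | 180 evaluable | 168 evaluable |
|---|---|---|
| 2.5 | 94% | 93% |
| 2.0 | 80% | 78% |
| 1.875 (three quarters of 2.5) | 75% | 73% |
| 1.25 (half of 2.5) | 42% | 40% |

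The difference detectable with 80% power is 1.99 points with 180 evaluable and 2.05 with 168. The plan's own pairing of 80% with 2.5 points is reached at about 7 patients per clinic (82%), so it understates the power for 2.5 at the planned size.

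**The case against.** There are five serious counter-arguments.

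- **The stated power is not attached to the 13%.** This is right. The 80% goes with the 2.5-point mean difference, and power at an assumed difference stays valid whatever the comparator is. A reader might infer that the stated power is wrong because the control is active. The article does not support that. What fails is the justification of the 13%, not the power statement.
- **The 13% may be a minimum important difference**, since it is called clinically significant. That reading is possible, but the same sentence ties the figure to brief intervention versus control, and nothing says it is the smallest worthwhile gain over mhGAP.
- **The source's control is not described.** This stands. It cannot be said from the article that those controls were untreated.
- **The effect need not be smaller.** This stands too. A reader might infer that the active control must shrink the difference and leave the trial underpowered. With 16 sessions in the experimental arm, the error could go either way.
- **The comparator is already named** in the Abstract, Background and Design. That is so, and it limits the wording point: the aim and hypothesis need aligning with what those sections already say.

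It can also be said that 2.0 points is worked back from the sample size. That is true. It says what the trial can detect, and whether 2.0 points over mhGAP matters still needs a clinical argument.

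**Conclusion.** The point holds in a limited form. The 13% is borrowed from a contrast that matches this trial on neither side and is expressed on an outcome that is not the primary one. It is therefore unsupported as the target for MI/CBT versus mhGAP. The size and direction of the resulting error cannot be derived from the article.

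On the primary AUDIT score the planned trial can detect about 2.0 points over mhGAP with 80% power and has about 93–94% at 2.5 points. Power falls to 73–75% at about 1.9 points and 40–42% at 1.25. The last two are sensitivity values, not estimates of how much benefit mhGAP captures. All these figures assume equal clinic sizes, a two-sided 5% test on clinic means, and that SD 4 and ICC 0.02 apply to the AUDIT measure analysed.

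**What to change.** **Sample size section.** Remove the 13% as the basis for the number of patients. State instead, on the AUDIT score: with 16 clinics, about 168 to 180 evaluable patients, within-clinic SD 4 and ICC 0.02, the trial has 80% power for a mean difference of about 2.0 points over adapted mhGAP, and about 93–94% at 2.5 points. Add the power at about 1.9 points (73–75%) and 1.25 points (40–42%), labelled as a sensitivity range. Add a sentence on why a difference of this order over mhGAP would matter.

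**Aims and Discussion.** Word the effectiveness aim and the hypothesis as reduction in AUDIT beyond adapted mhGAP. State that a non-significant result means no demonstrated added benefit over mhGAP.

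**Cost.** Text only: no added patients, visits or staff. The claim becomes narrower, and the power shown at small differences looks less favourable.

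### The figures 180 required, 30% attrition and 240 enrolled do not fit together: 240 leaves about 168 completers, though power is little affected

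*Protocol article*

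**What the plan says.** Everything relevant is in the Sample size section of the protocol article.

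- Requirement: "An estimated sample size of 180 patients (90 in the intervention group and 90 in the control group) will be required", to detect a 13% difference. The clustering allowance is already inside this number, "taking into account the design effect of 1.56".
- Attrition and enrolment: "Assuming an attrition rate of 30% (as identified in the pilot study), a total sample size of 240 will be required".
- Recruitment per clinic: "Fifteen participants will be randomly selected (with equal probability) at each clinic from a patient number list". With 16 clinics this is 240.
- Power: "A total of 16 clusters (8 clusters per group) to achieve 80% power to detect a mean difference of 2.5", "when the standard deviation within a cluster is 4 and the intra-cluster correlation are 0.02 and a significance level of 0.05".

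No other section gives a different attrition rate, or says that fewer than 180 completers would be enough.

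**The concern.** The step from 180 to 240 is presented as the allowance for 30% attrition, but 240 less 30% is below 180. By its own expected loss, taken from its own pilot, the trial would finish with fewer completers than it says it needs.

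A reader would believe that 30% loss is covered when the margin is really 25%, and anyone monitoring retention would work to the wrong tolerance. The 13% difference is the claim that the section ties to 180, so that claim is the one directly affected. The 80% power statement is attached to the 16 clusters and the 2.5-point mean difference, so it has to be checked separately.

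**Working it through.** **Inputs (all from Sample size):** 180 required after a design effect of 1.56; attrition 30%; 240 enrolled; 16 clinics, 8 per arm, 15 each; mean difference 2.5; within-cluster SD 4; ICC 0.02; significance level 0.05. The section does not say whether the test is one- or two-sided; two-sided is assumed here.

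**1. Trying to reproduce 240.** The valid inflation is N/(1 − d):

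180/(1 − 0.30) = 257.1, so 258 (129 per arm). The stated 240 is 18 lower.

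Two other routes do reach 240:
- 180/(1 − 0.25) = 240, the correct answer for 25% attrition.
- 180 × 1.30 = 234; 234/16 = 14.6, rounded up to 15 per clinic, and 15 × 16 = 240.

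**2. Equal recruitment per clinic.** 180/16 = 11.25 completers per clinic, and 11.25/0.70 = 16.07. Sixteen per clinic gives 256 × 0.70 = 179.2, just short. Seventeen gives 272 × 0.70 = 190.4. So 30% attrition with equal clinics needs 272.

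**3. What 240 delivers.** 240 × 0.70 = 168 (84 per arm, 10.5 per clinic). Shortfall: 180 − 168 = 12, and 12/180 = 6.7%. Largest attrition that keeps 180: 1 − 180/240 = 25%.

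**4. Power for 2.5 AUDIT points.**

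*(a) ICC 0.02, t distribution with 14 df.* Between-cluster variance = 16 × 0.02/0.98 = 0.327. SE = √[2(0.327 + 16/m)/8], where m is completers per clinic.

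*(b) Design effect 1.56.* SE = 4√(2 × 1.56/n), where n is completers per arm.

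| Method | 168 completers | 180 completers |
|---|---|---|
| (a) SE | 0.680 | 0.661 |
| (a) power, t with 14 df | 92.7% | 94.0% |
| (b) SE | 0.771 | 0.745 |
| (b) power, normal approximation | 90.0% | 91.9% |
| (b) power, t with 14 df | 85.4% | 87.7% |

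The loss is 1.3 to 2.3 points, and every figure is above 80%.

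**5. Power for a 13% difference.** The article gives no rate for either arm, so control rates of 5% to 50% are assumed, with the other arm 13 points higher. Effective n per arm is 84/1.56 = 53.8 against 90/1.56 = 57.7 (two-sided 5%, normal approximation, pooled variance under the null).

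| Assumed control rate | 168 | 180 | Loss (points) |
|---|---|---|---|
| 5% | 56.3% | 59.2% | 2.9 |
| 10% | 44.2% | 46.8% | 2.6 |
| 20% | 33.1% | 35.1% | 2.0 |
| 30% | 28.6% | 30.3% | 1.7 |
| 40% | 27.0% | 28.6% | 1.6 |
| 50% | 27.3% | 28.9% | 1.6 |

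The attrition step accounts only for the last column.

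**The case against.** The strongest reply is that nothing of substance depends on this. The only power stated is 80% for a 2.5-point difference. The primary outcome is the AUDIT score (Primary outcome tools; Outcome measures), and at 168 completers power for that difference is still well above 80%. This stands, and it sets the severity.

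A second reply is that 168 is not the number analysed. Participant level includes every participant in the analyses, and Analysis approach plans GEE partly because follow-up data will be missing. Someone lost after 3 or 6 months still contributes earlier visits, and the article does not say when attrition occurs. This also stands: 168 should be read as expected completers. It does not rescue 240, because the section itself adds an attrition allowance and so treats 180 as the number needed after loss. Including incomplete participants does not recover missing AUDIT scores.

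Two other defences fail. Rounding does not explain the gap, because rounding to equal clinics goes up, to 272. The design effect does not explain it either, because the 180 already contains it. Nor is this a detail left to a fuller document: the calculation is stated here, with a result that does not follow.

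**Conclusion.** The inconsistency is certain and follows from the printed figures alone: 180, 30% and 240 cannot all hold. The shortfall at the protocol's own attrition rate is 12 completers (6.7%). It costs about 1 to 2 points of power for the 2.5-point AUDIT difference and about 2 to 3 points for the 13% difference. The first figure assumes a two-sided test, the second also the range of control rates shown. Severity: minor.

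Three stronger readings are not supported:

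- **That the error leaves the trial underpowered or its stated power overstated.** The stated 80% is met at 168 under every method above.
- **That the low power for a 13% difference is caused by the attrition step.** It is about as low at 180. With the design effect of 1.56 and the same assumed rates, 80% power would need 147 to 359 per arm. That is a separate question about where 180 comes from.
- **That the authors multiplied by 1.3 instead of dividing by 0.7.** This is possible, but the article does not show its method, and a 25% allowance gives 240 exactly.

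**What to change.** Do not keep 180, 30% and 240 together. Replace the attrition sentence with one of these:

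- *240 enrolled (15 per clinic); at 30% attrition about 168 (84 per arm) are expected to complete follow-up*, with power quoted at 168; or
- a statement that 240 enrolled preserves 180 completers only if attrition is no more than 25%.

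The wording should refer to completing follow-up, not to being analysed, so that it agrees with Participant level and Analysis approach.

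Either version costs one sentence and adds no patients. Keeping both 180 and 30% would instead mean enrolling 258, or 272 at 17 per clinic; the small loss of power does not by itself call for that.

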### Management of missing data

Intention to treat will be the principle of statistical analysis.

### Clinic level

All clinics randomized at cluster level will be analysed by the treatment arm allocated at randomization.

### Participant level

All participants in the study will be included in the analysis of primary and secondary outcomes.

### Analysis approach

Data will be analysed using STATA Version14 [59]. Primary and secondary outcomes will be measured at four time points: baseline, 3, 6, and 12 months. To account for the stratified cluster trial design, the repeated binary and linear nature of the primary and secondary outcomes, as well as missing data at follow-up, a Generalized Estimation Equations (GEE) approach will be used. Descriptive statistics will be computed for baseline and follow-up assessments. The mean AUDIT scores will be compared using student t-tests. Multilevel logistic regression will be performed for binominal and multilevel linear regression for continuous variables.

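### GEE is given the job of handling clinic clustering and missing follow-up, but with 16 clinics it needs a small-sample correction and does not in itself deal with dropout; the mixed model already listed should be named as primary

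*Protocol article*

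**What the plan says.** Analysis approach assigns three jobs to one method. To deal with the cluster design, the repeated outcomes and incomplete follow-up, "as well as missing data at follow-up, a Generalized Estimation Equations (GEE) approach will be used". The same section then lists Student t-tests for mean AUDIT, and multilevel linear and logistic regression.

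The Sample size section adds "Analysis of covariance (ANCOVAs) and mixed effects linear regression models will be performed for all continuous variables", and says that every analysis will allow for clustering within clinics. It expects 30% attrition.

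The section headed Management of missing data has one sentence: "Intention to treat will be the principle of statistical analysis". Participant level adds: "All participants in the study will be included in the analysis of primary and secondary outcomes".

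No sentence says which of these analyses decides the AUDIT result. No variance estimator, reference distribution, working correlation, weighting or missing-data assumption is given for GEE.

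**The concern.** Two things that the text expects of GEE are not delivered by GEE as such.

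**Clustering.** The usual GEE tests rely on a large number of clusters. Here there are 16, 8 per arm. The uncorrected sandwich variance is too small on average at that number, and a normal reference ignores the uncertainty in the variance. Both push the true error rate above 5%.

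**Missing follow-up.** Unweighted GEE uses the visits that are present. If dropout depends on earlier AUDIT scores, it is consistent only if that dependence runs through covariates in a correct mean model or if the working correlation is correctly specified. Intention to treat fixes the arm in which a participant is counted; it supplies no method for an absent score. Someone with no follow-up AUDIT adds nothing to a GEE of follow-up scores, whatever the analysis set is called.

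Arm-specific dropout is plausible here. The intervention has 16 sessions; the control session lasts about an hour and is given again at 3 and 6 months; participants are not blinded. The stakes are a false-positive rate nearer one in eleven than one in twenty, and a treatment effect that could be shifted by selective loss.

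**Working it through.** **Inputs.** From Sample size: "A total of 16 clusters (8 clusters per group) to achieve 80% power to detect a mean difference of 2.5"; "the standard deviation within a cluster is 4"; "assumed the intra-cluster correlation in this study to be 0.02"; "a significance level of 0.05" (sidedness is not stated; two-sided assumed); 15 recruited per clinic; 30% attrition. From Analysis approach: GEE, with visits at baseline, 3, 6 and 12 months.

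**The plan's own figure.** The 80% power does not reproduce. At 15 per clinic the design effect is 1 + 14 × 0.02 = 1.28 and power is about 99% (98% on 14 degrees of freedom). At 10-11 analysed per clinic it is 95-97% (92-94%). That is a separate matter, and nothing below depends on it.

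**Type I error, closed form.** With k = 8 equal clinics per arm, the uncorrected sandwich variance of the arm difference is (k − 1)/k = 7/8 of the unbiased between-clinic variance. The unbiased statistic follows t on 16 − 2 = 14 degrees of freedom. The true size of a nominal 5% test is therefore P(|t14| > c):

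| Variance and reference | c | True size |
|---|---|---|
| Uncorrected sandwich, normal | 1.960 × √(7/8) = 1.833 | 8.8% |
| Scaled by 16/15, normal | 1.960 × √(7/8 × 16/15) = 1.894 | 7.9% |
| Unbiased variance, normal | 1.960 | 7.0% |
| Uncorrected sandwich, t on 14 df | 2.145 × √(7/8) = 2.006 | 6.5% |
| Unbiased variance, t on 14 df | 2.145 | 5.0% |

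**Type I error, simulation.** Exchangeable linear GEE clustered on clinic, 16 clinics of 15, 30% lost completely at random, baseline covariate, 6,000 runs at each ICC (0.01, 0.02, 0.05):

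- uncorrected sandwich, normal: 9.2%, 8.8%, 9.1%
- 16/15 scaling, normal: 8.0-8.4%
- model-based errors, normal: 8.3-8.8%
- uncorrected sandwich, t on 14 df: 6.5-7.0%
- Mancl-DeRouen sandwich: 5.3-5.8% with normal, 3.6-4.2% with t on 14 df

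The Monte Carlo standard error is about √(0.09 × 0.91/6000) = 0.4 percentage points. The inflation is thus not peculiar to the sandwich, and a bias-corrected variance removes most or all of it.

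**Missing data.** Large-sample simulation with no true effect, SD 4, 30-35% lost by 12 months, and GEE of the 3, 6 and 12-month scores adjusted for baseline. The dropout models and within-person correlations are assumptions; the protocol gives none. Bias is in AUDIT points at 12 months, and negative values favour MI/CBT.

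| Dropout | True correlation | Independence GEE | Exchangeable GEE |
|---|---|---|---|
| Completely random | exchangeable | 0.01 | 0.00 |
| Previous AUDIT, same in both arms | exchangeable | −0.02 | −0.02 |
| Previous AUDIT, opposite by arm | exchangeable | −0.67 | −0.03 |
| Previous AUDIT, same in both arms | decaying over visits | 0.00 | −0.01 |
| Previous AUDIT, opposite by arm | decaying over visits | −0.72 | +0.22 |
| Baseline AUDIT, opposite by arm | exchangeable | −0.01 | −0.01 |
| Baseline AUDIT, opposite by arm | decaying over visits | +0.51 | +0.67 |

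In the last row the fitted model held the baseline effect constant over visits, which is wrong when the correlation decays. The covariate exception therefore needs a correct mean model. Against the 2.5-point target, 0.22/2.5 = 9% and 0.72/2.5 = 29%. The direction of the bias is not fixed.

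**The case against.** The strongest reply is that the protocol article never specifies the analysis to which the 8-9% belongs. It names no sandwich variance, no absence of correction and no normal reference; an article may leave these to the full protocol or the SAP, which are not shown. That stands. The figure describes GEE used without a small-sample correction, and it cannot be reported as the trial's error rate.

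Three stronger readings are tempting, and the documents do not support them.

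- A reader might infer that GEE is valid here only if dropout is completely random. That is too absolute. Dropout through correctly modelled covariates is allowed, and a correctly specified exchangeable GEE was nearly unbiased (−0.03) even under opposite outcome-dependent dropout.
- A reader might infer that taking the participant as the GEE panel would ignore the clinics. Sample size says that all analyses allow for clustering within clinics, which excludes that reading. A participant-level working correlation can also be combined with a clinic-level jackknife or bootstrap variance.
- A reader might infer that the treatment effect will be biased. The bias needs a dropout mechanism that differs by arm. Unequal session burden makes that plausible but does not establish it.

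It is also fair that GEE is not the only method listed: the mixed and multilevel models are valid under missing at random when correctly specified. But Analysis approach assigns clustering and missing data to GEE, and nothing says that the mixed model takes precedence. Their presence makes the repair easy without making it.

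**Conclusion.** The point holds in conditional form. The plan states that GEE accounts for missing follow-up, and GEE in itself does not. The plan relies on GEE for clustering with 16 clinics, where the normal-reference test without small-sample correction has a true size of about 8-9%, falling to about 4-6% with a bias-corrected sandwich. With several competing analyses and none governing, the AUDIT conclusion could rest on the version with the inflated error rate.

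The error-rate figures assume a two-sided 5% test and, for the closed form, equal clinic sizes. They changed little across ICC 0.01-0.05 with unequal numbers retained. The bias range of about 0.2-0.7 AUDIT points shows what could happen under assumed arm-specific dropout and is not a forecast; it is about 0 if the mechanism is the same in both arms. This should be corrected, but it does not invalidate the design.

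**What to change.** In Analysis approach, name the already-listed linear mixed model as the single primary analysis of AUDIT:

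- all visits, with baseline AUDIT, whose effect is best allowed to differ by visit (see the last row of the bias table);
- a random effect for clinic;
- a within-participant correlation that is not forced to be exchangeable, for example unstructured over visits, because a wrong exchangeable structure left a bias of 0.22 in the check above;
- REML with Kenward-Roger or Satterthwaite degrees of freedom.

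State missing at random as the assumption of this model, in place of the statement that GEE accounts for missing data. Keep GEE, if at all, as a sensitivity analysis clustered on clinic with a small-sample correction, noting that Mancl-DeRouen with t on 14 df was somewhat conservative (3.6-4.2%). A delta-adjusted sensitivity analysis for dropouts is optional.

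The cost is wording and minor programming. With about 14 degrees of freedom, confidence intervals are wider than those from GEE with a normal reference by 2.145/1.894 = 1.13 (16/15 scaling) to 2.145/1.833 = 1.17 (uncorrected), that is 13-17%. This is the width that a true 5% error rate requires.
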